## Discussion

The study has been initiated as planned on august 01 2007. One interim analysis advised continuation of the trial. The study will be completed in February 2011. A significant difference in the safety and/or efficacy endpoints will provide important evidence for optimizing clinical patient care. Also a neutral result will provide important insight, as this would mean that clinicians can safely withhold PN in all comparable patients during the first week of ICU stay, which has an impact on expenses for critical care.

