### Rationale of the study

In view of the 2 different practice guidelines widely adopted based upon strong expert opinion but in the absence of high level evidence, there is need for an adequately powered randomized controlled trial comparing the two nutritional practices.

In a context of prevention of hyperglycemia and while avoiding overfeeding, a strategy based on early PN completing EN up to a calculated caloric and protein target (further referred to as "early PN") could be superior to withholding PN during the first week of critical illness (further referred to as "late PN") by preventing weakness and enhancing recovery. Alternatively, withholding PN during the first week of critical illness ("late PN") while advocating early EN may shorten ICU and hospital stay by avoiding complications of early PN. Finally, clinical equivalence of the 2 feeding strategies would generate evidence in favor of withholding PN for one week in ICU in view of the cost of this intervention. (Figure 1)

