A priori defined subgroup analyses will be performed for BMI and NRS subcategories. These subgroup analyses are based on the rationale that BMI has been reported to be associated with different risk of outcome in different types of ICU patients which may be due to different handling of nutritional substrates [36-38]. This risk appeared different for patients with overweight or obesity (BMI 25 to <40) versus all other BMI categories (undernourished and normal BMI [BMI <20 and BMI 20-<25] or morbid obesity [BMI ≥ 40]). Therefore BMI will be dichotomized as such to optimize the power of this subgroup analysis. Also patients at higher risk of malnutrition may respond differently to the feeding strategies. Therefore, in this subgroup analysis, NRS will be dichotomized separating the highest risk patients [NRS ≥ 5] from the moderate risk patients [NRS 3 and 4]. Another a priori defined subgroup analysis will be performed for patients admitted to ICU after emergency or elective cardiac surgery as compared with all other patients. The shorter time in ICU of this subgroup may result in the early PN group receiving predominantly extra glucose 20% infusion, without lipids and amino-acids, as compared with the glucose 5% in the late PN group, which may evoke a different response than the full week combined parenteral nutrition. As sepsis is known to aggravate the metabolic disturbances evoked by early PN, a priori subgroup analysis is planned for patients with and without sepsis upon admission. These a priori defined subgroup analyses will be performed for the primary and safety endpoints without correction for other variables. To test for interaction between the identified subgroups and the studied intervention, a multivariable analysis (logistic regression or proportional hazard analysis as appropriate) will be performed for each subgroup variable separately and with the subgroup variable, the intervention and their interaction in the model. The interaction will be tested at a significance level of 0.1.

The first clinical report will analyze the impact of the nutritional strategies on safety (among which mortality), primary and secondary efficacy endpoints.

For all endpoints, differences will be considered statistically significant whenever the p-value reaches 0.05 or lower without correction for multiple testing.

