### Sample size calculation

The sample size was calculated in order to detect, with at least 80% power and 95% certainty, an increase or decrease in average duration of ICU stay with one day [from a baseline assumed ICU stay of 8 ± 13 (mean ± SD) days and a median of 4 days assuming log-normal distribution; power calculated using one-tailed Student's t-test using the mean and SD for an increase and a decrease with 1 day and confirmed with two-tailed Student's t-test after log transformation]. To concomitantly detect with at least 70% power and 95% certainty an ICU mortality increase or decrease of 3% (assuming a baseline mortality of 20% anticipating a Medical-ICU/Surgical-ICU patients fraction of 25/75%; power calculated with two-tailed chi-square testing), a sample of 4640 (patients 2320 per arm) was considered necessary. We plan to calculate the true power of the study for detection of any eventual smaller difference in these outcomes.

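### The Discussion reads a neutral result as showing that PN can be safely withheld, but the trial tests only for differences and sets no limit for judging its confidence intervals

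*Protocol article*

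**What the plan says.** The Discussion of the protocol article looks ahead to a non-significant outcome: "Also a neutral result will provide important insight, as this would mean that clinicians can safely withhold PN in all comparable patients", for the first week in ICU. The Rationale of the study lists a related possibility, that "clinical equivalence of the 2 feeding strategies would generate evidence in favor of withholding PN for one week in ICU", and ties it to the cost of PN.

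The statistical sections contain only a criterion for differences. General rules of the statistical analyses states: "For all endpoints, differences will be considered statistically significant whenever the p-value reaches 0.05 or lower without correction for multiple testing". Sample size calculation is likewise framed as detection. For mortality the aim is "To concomitantly detect with at least 70% power and 95% certainty an ICU mortality increase or decrease of 3" percent, and the result is that "a sample of 4640 (patients 2320 per arm) was considered necessary".

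Two planned items bear on a neutral result. Safety endpoints promises odds ratios with 95% confidence intervals for mortality, together with Cox analysis of survival to day 90. Sample size calculation adds: "We plan to calculate the true power of the study for detection of any eventual smaller difference in these outcomes". Neither is tied to a limit on how much excess mortality would still count as safe.

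**The concern.** A test for a difference that does not reach 0.05 shows that the data are compatible with no effect. It does not show that a relevant harm has been excluded. To call withholding PN safe, one needs an upper bound on the excess mortality and a stated value which that bound must not cross. The article supplies the first through its confidence intervals, but not the second.

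The claim at stake is about mortality, it is meant to guide practice in all comparable patients, and a neutral outcome is one that the authors expect may occur. If the Discussion sentence carries over into the report, a trial whose interval still includes an excess larger than the one it was sized to find could be presented as evidence of safety.

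**Working it through.** **Inputs, all from Sample size calculation.** Baseline ICU mortality: "assuming a baseline mortality of 20% anticipating a Medical-ICU/Surgical-ICU patients fraction of 25/75" percent. Target change: 3 percentage points either way. Test: "power calculated with two-tailed chi-square testing", taken at two-sided 0.05. Sample: 2320 per arm, allocated 1:1.

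**Step 1. Reproduce the stated power.** For p1 = 0.20 and p2 = 0.23, the mean proportion is 0.215.
- SE under the null = √(2 × 0.215 × 0.785 / 2320) = 0.01206
- SE under the alternative = √((0.20 × 0.80 + 0.23 × 0.77) / 2320) = 0.01205
- Power = Φ((0.03 − 1.96 × 0.01206) / 0.01205) = Φ(0.53) = 70.1%

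The number needed for 70% power is 2315 per arm, so the stated 2320 reproduces. A fall to 17% has 74.9% power. A continuity correction lowers the 70.1% to 68.9%, which changes nothing here.

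**Step 2. Chance that this one test is non-significant when late PN does raise mortality.** The same formula gives:

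| True ICU mortality, early v late | Power | Non-significant |
|---|---|---|
| 20% v 23% | 70.1% | 29.9% |
| 20% v 22% | 38.7% | 61.3% |
| 20% v 21% | 13.2% | 86.8% |

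These figures describe a single unadjusted test of ICU mortality.

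**Step 3. What a non-significant result can still include.**
- SE of the difference with 20% in both arms = √(2 × 0.20 × 0.80 / 2320) = 0.01174, or 1.17 points
- 95% half-width = 1.96 × 1.17 = 2.30 points
- An observed excess just under 2.3 points is non-significant; its upper limit is about 2.3 + 2.3 = 4.6 points

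That exceeds the 3 points for which the trial was sized.

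**Step 4. What the existing sample could show against a margin.** The documents give no margin, so a range is assumed. With true mortality of 20% in both arms, the chance that the upper limit of the two-sided 95% interval falls below margin m is Φ(m / 1.174 − 1.96):

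| Assumed margin (points) | Power with 2320 per arm |
|---|---|
| 2 | 40% |
| 2.5 | 57% |
| 3 | 72% |
| 4 | 93% |

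With a 3-point margin, the largest observed excess that would still pass is 3 − 2.30 = 0.70 point. Under the difference test, an excess up to about 2.3 points counts as neutral. On the odds-ratio scale that the plan reports, 23% v 20% is (0.23/0.77) / (0.20/0.80) = 1.19.

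**The case against.** The strongest reply is that the sentence is a closing remark and not an analysis rule. This stands. A reader might infer that the statistical analysis plan formally declares safety or equivalence when p exceeds 0.05, but no statistical section says so. The fault lies in the stated interpretation, together with the lack of anything in the statistical sections to restrain it.

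Second, a reader might infer that retrospective power is the only help planned for a neutral result. That is not so. Safety endpoints already plans odds ratios with 95% confidence intervals, and these do bound the effect. What is missing is the value to compare them with. Moreover, the sentence on true power can be read as the power to detect smaller differences given the actual event rates and variance, which is harmless in itself. It becomes a problem only if it stands in for the interval.

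Third, it is tempting to quote 30%, 61% and 87% as the chance that the trial would wrongly declare PN safe to withhold. The Discussion contrasts a neutral result with a significant difference in safety or efficacy endpoints, and there are several of these, analysed with and without correction. If neutral means non-significant on all of them, the chance under a true harm cannot exceed the single-test figure and is probably lower. In addition, excesses of 1 and 2 points would lie inside a 3-point margin, so the 61% and 87% figures do not describe errors by that standard.

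Fourth, the Rationale gives limited support. It is conditional on equivalence and argues from cost; not using a costlier addition without shown benefit is a defensible position. It simply never says how equivalence would be established.

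What remains after all this is the Discussion sentence itself. It moves from neutral to safe, and the design does not support that step.

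**Conclusion.** Wrong as written. The trial is designed and tested for differences, and the Discussion draws a safety conclusion from not finding one. On the plan's own assumptions (20% ICU mortality, 2320 per arm, two-sided 0.05), a true 3-point rise would leave a single unadjusted ICU-mortality test non-significant in about 30% of trials. A non-significant result could have an upper 95% limit of about 4.6 points. Both figures depend on the assumed 20%, since a different event rate changes the standard error.

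The documents do not support a claim that the sample size or the planned tests are wrong: the stated size reproduces. Nor do they fix 3 points as an acceptable harm. It is the difference chosen for detection, and its use as a margin would need its own clinical justification.

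**What to change.** 1. Reword the Discussion so that a non-significant result is not in itself taken as safety or equivalence, and make the Rationale consistent by saying how equivalence would be judged.
2. Before unblinding, state that withholding PN is called safe with respect to mortality only if the upper limit of the two-sided 95% interval for late minus early lies below a pre-stated, clinically justified margin. Otherwise the result is called inconclusive. Name the mortality endpoint to which this applies. The plan's 3 points for ICU mortality is one candidate, with about 72% power if there is no true difference. Because the DSMB saw unblinded mortality at the interim analysis, the margin should be set by people who did not.
3. For ICU stay, base any statement of equivalence on the confidence interval of the hazard ratio from the planned Cox analysis of time to discharge alive. A one-day limit would suit a difference in means, which is not the primary analysis.
4. Keep the calculation of power for smaller differences, if wanted, as a description only. It should not replace the interval when a neutral result is interpreted.

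The cost is wording in the plan and report, plus agreement on a margin and an interval for the risk difference alongside the odds ratio. No change to sample size, conduct or data collection is needed. The real downside is that a neutral result may have to be called inconclusive: 80% power to exclude 3 points would take 5582 patients in total, against the 4640 planned.

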## Abbreviations

6MWD: 6MWD; ADL: Activities of Daily Life; APACHE: Acute Physiology And Chronic Health Evaluation; BMI: Body Mass Index; CRF: Case Report Form; DSMB: Data Safety Monitoring Board; EN: Enteral Nutrition; ICU: Intensive Care Unit; IRB: Institutional Review Board; KWS: Clinical Working Station; NRS: Nutritional Risk Screening; PDMS: Patient Data Management System; PN: Parenteral Nutrition; RCT: Randomized Clinical Trial; RRT: Renal Replacement Therapy; SD: Standard Deviation.
